Patient participants will be identified using an automated practice database search strategy designed by the research team. The practice administrative team will use this ‘flag’ to identify ten consecutive potential participants with pre-booked consultations with each of the three recruited GPs. Random sampling of participants is not required as the clinical presentations, and therefore the nature of the decision-making between consecutive consultations, is expected to be random. A total of 180 (minimum 120) potential patients will be identified across 6 practices, with the aim of recruiting at least half.

The sample size is sufficient to compare between-group differences in quantitative feasibility objectives such as recruitment rates and data collection procedures including the completeness of participant questionnaires. This sample size also allows the estimation of standard deviations for the clinical outcome measures being tested. In addition, it is sufficient to obtain a purposively selected sub-sample of participants for process evaluation interviews, to achieve the qualitative feasibility objectives.

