### Randomisation and blinding

The study will use a cluster randomised design. Clusters will be defined at practice level, with practices randomised 1:1 to usual care or to the intervention (90 patients per arm) following recruitment. Block randomisation will be stratified by site; two practices in inner city Plymouth, two practices from Exeter and two from rural Devon.

Randomisation will be conducted by an independent statistician who is blinded to the identity of practices. Blinding of the research team to outcome assessment will not be possible due to resource availability. Blinding of participants is unlikely to be achievable as participants in the intervention arm are likely to be aware that they are receiving more than standard ‘usual care’.

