**Baseline**					
Practice characteristics (list size, location, deprivation)	Prior to randomisation	Practice and Association of Public Health Observatories website	6 practices	Categorical, nominal/ordinal.	Frequencies, to report data descriptively. Logistic hierarchical modelling to estimate between group differences^a^ (random effect on cluster, adjustment for practice location).
Patient age, gender, ethnicity, self-reported health status	Prior to index consultation	Pre-consultation postal questionnaire	180 patients	Categorical, nominal/ordinal.	Frequencies, to report data descriptively. Logistic hierarchical modelling to estimate between group differences (random effect on cluster, adjustment for practice location).
Patient deprivation data from patient postcodes	Following return of patient pre-consultation questionnaires and consent forms	Practice records mapped to the Index of Multiple Deprivation	180 patients	Continuous (IMD scale)	Mean and standard deviation, to report data descriptively. Linear hierarchical modelling to estimate between group differences^a^ (random effect on cluster, adjustment for practice location).
GP age, gender, ethnicity, time since qualification	Prior to index consultation	GP practices and General Medical Council GP registry	18 GPs	Categorical, nominal/ordinal	Frequencies, to report data descriptively. Logistic hierarchical modelling to estimate between group differences^a^ (random effect on cluster, adjustment for practice location).
Patients’ preferences for involvement in decision-making.	Prior to index consultation	Patient pre-consultation postal questionnaire	180 patients (90 per arm)	Ordinal (6 point Likert scale).	Frequencies, to report data descriptively. Logistic hierarchical modelling to estimate between group differences^a^ (random effect on cluster, adjustment for practice location).

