Participant experiences of the intervention, participants experiences of the study	Following receipt of participant post-consultation questionnaires and consent forms	Interviews with the participants from practices assigned to the intervention	9 GPs, 15 patients	Audio-recordings for qualitative analysis	Both deductive and inductive approaches to thematic analysis

^a^Between group differences will be reported using the appropriate outcome metric with 95% confidence intervals; no p-values will be reported in this feasibility study

Using an ‘intention to treat’ approach, participants will be analysed according to their randomised allocation irrespective of intervention actually received. However, all participants will be considered adherent by definition of the protocol. There is no mechanism by which participants in the control group could receive the intervention.

An intra-cluster correlation coefficient (ICC) will be calculated within each arm (intervention and control) for academic purposes; however, this will not be used to calculate a sample size for the future definitive trial; an estimated ICC, calculated from a large relevant routine dataset, will instead be sought [40].

The appropriateness of the outcome measures for use in a future, definitive trial of the intervention will be evaluated. The consistency with which certain outcome measures (e.g. OPTION(5), CollaboRATE, and those items taken from the GPPS survey) perform with the study population, when compared with previous performance in existing literature, will be reviewed. Findings will also be considered in the context of the internal consistency of performance of these measures within the participant sample. Consideration will be given as to whether the outcome measures chosen are sensitive to the effects of the intervention in the context of older people with multimorbidity in primary care, or whether there is a need for development of new measures.

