#### Preliminary evaluation of participant responses to the intervention

The intended sample size is sufficient to estimate standard deviations in our intended primary outcome, ‘ratings of shared decision-making during the consultation from an observer perspective’, for the intervention and control group. This outcome data will be obtained from OPTION(5) ratings of video-recorded consultations. No formal power calculations will be carried out and hypothesis testing will not be appropriate [47].

The observer OPTION(5) scores (Elwyn 2014) and the patient and GP ratings of shared decision-making, based on collaboRATE (Elwyn 2014), will be analysed using hierarchical linear modelling with a random effect on cluster. Patient and GP collaboRATE scores will be compared using logistic regression; modelling patient scores as the outcome and GP scores as the explanatory variable, providing preliminary data on whether patient and GP perceptions are congruent.

Patients vary in their pre-existing preferences for involvement in decision-making about their healthcare (Butterworth 2013 [50];). A secondary analysis with adjustment for patients’ reported preference for shared decision-making will provide a preliminary indication as to whether patients’ pre-existing preferences influence the effect of the intervention.

The participant population will be ‘all randomised’ and the analysis strategy will be ‘intention to treat’. There are no plans for interim analysis.

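### Adjusting for patients' preference for involvement cannot show whether preference changes the intervention effect; an exploratory arm-by-preference term, or a reworded aim, is needed

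*Protocol article*

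**What the plan says.** Under Preliminary evaluation of participant responses to the intervention, one sentence of the protocol article gives both method and purpose. The method is "A secondary analysis with adjustment for patients’ reported preference for shared decision-making"; the purpose is that this "will provide a preliminary indication as to whether patients’ pre-existing preferences influence the effect of the intervention". The outcomes concerned, observer OPTION(5) and the patient and GP collaboRATE ratings, "will be analysed using hierarchical linear modelling with a random effect on cluster".

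Table 4 lists preference only among the baseline variables, as "Ordinal (6 point Likert scale", with a descriptive summary and a between-group comparison. Its outcome models contain a random effect on cluster and adjustment for practice location. The article names no arm-by-preference term, stratified estimate or subgroup analysis.

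On inference, "No formal power calculations will be carried out and hypothesis testing will not be appropriate", and the footnote to Table 4 says "Between group differences will be reported using the appropriate outcome metric with 95% confidence intervals; no p-values will be reported in this feasibility study".

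**The concern.** The stated method and the stated purpose are different analyses. Asking whether preference influences the effect is asking whether the arm difference varies with preference. A model with arm and preference as main effects assumes that it does not.

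The question matters for this intervention. The patient tool described in Table 2 is built around a spectrum of preferences for involvement, with phrases for asking for a part in decisions and for declining one. Whether the effect differs along that spectrum is useful to know when designing the definitive trial. Carried out as written, the analysis would leave it unanswered while the text says that it has been addressed.

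This is not a detail left to an unseen analysis plan: the article states both the method and the aim, and they do not match.

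**Working it through.** **Inputs from the article.** Six practices, "practices randomised 1:1 to usual care or to the intervention (90 patients per arm) following recruitment"; "A total of 180 (minimum 120) potential patients will be identified across 6 practices, with the aim of recruiting at least half". The counts reproduce: 6 practices × 3 GPs × 10 patients = 180, or 90 per arm; 6 × 2 × 10 = 120 at the minimum. Recruiting half gives 90 or 60 in total. No power figure is stated, so there is none to reproduce.

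**Step 1: what the adjusted model estimates.** Write the planned model as Y = a + b·arm + c·preference (plus site and cluster terms). The arm difference at preference p is (a + b + c·p) − (a + c·p) = b, for every p. Variation with preference needs d in Y = a + b·arm + c·preference + d·arm·preference, where the arm difference is b + d·p.

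**Step 2: what a change on adjustment means.** In least squares, unadjusted b − adjusted b = c × (arm difference in mean preference), and the hierarchical model behaves in much the same way. A shift therefore reflects a difference in reported preference between the arms: imbalance across six practices (including selective recruitment after allocation), or an intervention effect on reported preference. Neither is effect modification.

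**Step 3: two truths that the adjusted model cannot separate.** Put preference on a scale with mean 0 and SD 1, with equal arms.

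- Truth A: arm effect 0.5 everywhere, preference slope 0.6 in both arms.
- Truth B: arm effect 0.5 at mean preference, slope 0.3 under usual care and 0.9 under the intervention, so d = 0.6.

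The pooled slope under B is (0.3 + 0.9)/2 = 0.6, so on average both truths give b = 0.5 and c = 0.6. If the six levels are equally common, their SD is √(35/12) = 1.708 and the end levels lie at ±2.5/1.708 = ±1.464. The effect under B then runs from 0.5 − 0.6 × 1.464 = −0.38 to 0.5 + 0.6 × 1.464 = 1.38; under A it is 0.5 throughout.

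**Step 4: simulation.** 4,000 runs per setting; six clusters in three sites, arm assigned by cluster, equally common preference levels, least-squares fits with site terms. Assumed, not in the article: outcome SD 1 around the mean, ICC 0.05, arm effect 0.5 SD, preference effect 0.3 SD, and no effect of arm on preference. Mean estimates:

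| N | True interaction | Unadjusted arm effect | Adjusted arm effect | Interaction estimate |
|---|---|---|---|---|
| 180 | 0 | 0.496 | 0.498 | 0.000 |
| 180 | 0.3 | 0.500 | 0.499 | 0.298 |
| 180 | 0.6 | 0.495 | 0.495 | 0.599 |
| 90 | 0 | 0.499 | 0.499 | −0.004 |
| 90 | 0.3 | 0.505 | 0.502 | 0.303 |
| 90 | 0.6 | 0.504 | 0.503 | 0.599 |

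**Step 5: precision of the interaction.** With equal arms and outcome SD 1, its standard error per SD of preference is about √(4/N) = 2/√N, and the 95% half-width is 1.96 × 2/√N. The simulated standard deviations agree: 0.151 against 0.149 at N = 180, and 0.214 against 0.211 at N = 90. From lowest to highest level is 5/1.708 = 2.93 SD of preference, so the half-width for the difference in effect between the two ends is 2.93 times as large.

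| N | Half-width per SD of preference | Half-width, lowest to highest level |
|---|---|---|
| 180 | 0.292 | 0.86 |
| 120 | 0.358 | 1.05 |
| 90 | 0.413 | 1.21 |
| 60 | 0.506 | 1.48 |

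Units are outcome SDs. The formula lets the interaction slope be the same in all practices; if it varies, the intervals are wider.

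**Step 6: when preference is measured.** The section The intervention has the tool mailed before the index consultation, and the footnote to Table 2 adds a waiting-room poster. Recruitment procedures has the pre-consultation questionnaire handed out on arrival in the waiting room, whereas Table 4 calls it postal. On the first account, intervention patients may report a preference after seeing a tool about preferences.

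**The case against.** The best defence is that adjustment is what was meant and the purpose is loosely worded. Under Comparisons with existing literature, the article reports a review's advice to correct results for patients' preferences, which is what adjustment does. On that reading the model is sound and only its description is wrong. This is why rewording the aim is an acceptable remedy. It does not save the sentence as it stands, which speaks of influencing the effect of the intervention.

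A reader might go further and infer that the planned analysis would show preference not to matter, perhaps hiding harm in patients who do not want involvement. The documents do not support that. A main-effects model is silent on modification; it is not evidence of none, and the wrong conclusion would need a misreading. Nothing in the article suggests harm at low preference, and the tool serves patients who wish to decline involvement as well as those who want it. Interviewees in intervention practices are also sampled for variety in preference, which partly complements the analysis without replacing it.

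It can also be said that the interaction will be too imprecise to settle anything. That stands: at these sample sizes the interval could include both no modification and a meaningful amount. Calling the result preliminary excuses imprecision, but not estimating a different quantity. The timing problem stands too: an interaction with a preference that the tool may have altered would not cleanly show modification by preference held beforehand.

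**Conclusion.** The point holds at moderate severity. The analysis as described cannot answer the question set for it, and nothing elsewhere in the article supplies the missing term. That conclusion is algebraic and does not depend on the simulation values. The precision figures do rest on assumptions: equal arms, equally common preference levels, outcome SD 1 and a common interaction slope across practices.

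It would be an overstatement to infer that the sentence undermines the trial's main conclusions. The Objectives call responses to the intervention tentative and preliminary, and the analysis is secondary. The progression criteria cover recruitment, questionnaire response, consent to case-note review and usable video only. No feasibility decision changes if the sentence stays.

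**What to change.** Add arm × preference, with preference as a linear score over its six levels, to the hierarchical OPTION(5) and collaboRATE models. Report the interaction, and the estimated effects at a low and a high level chosen in advance, with 95% confidence intervals and no p-values, labelled exploratory.

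State two limits with it: the intervals will be wide, and preference in the intervention arm may be reported after exposure to the patient tool. Reconcile Recruitment procedures with Table 4 on how and when the questionnaire reaches patients, because that decides how far the variable can be read as a prior preference. The between-group comparison of preference already planned in Table 4 should be read alongside, since a difference there could come from imbalance or from exposure.

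If the main-effect model is kept, describe it only as a preference-adjusted effect estimate. If no interaction is fitted, reword the aim to say that.

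The cost is one model term and a few sentences, or one reworded sentence. No extra patients or data are needed; the price is an estimate that will be imprecise.

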### Process evaluation using qualitative methods

A qualitative interview study, embedded within the feasibility trial with data integration.

Fifteen patients from intervention practices will be sampled and twice this number will be approached. Patients will be selected purposively and iteratively, using questionnaire data to ensure heterogeneity by age, sociodemographic characteristics, health status and preference for shared decision-making (Coyne 2008). Patients will be contacted by telephone to arrange an interview. All GPs in the intervention group will be invited by email. The sample size will be reviewed when assessing thematic saturation [22].

Following receipt of post-consultation participant questionnaires, semi-structured interviews aided by a topic guide will be digitally audio recorded, transcribed and supported by field notes. Participants will be encouraged to discuss their own ideas in order to collect fresh data without the influence of the researcher (Britten et al. 1995). Data will be collected regarding:

Participant experiences of the intervention
Acceptability of the interventionInfluences for intervention implementation and integration into normal practiceWhether participants perceive the intervention to be effective

Participant experiences of the study
How study participation was experiencedWhether study participation induced behaviour change not prescribed by the intervention

Audio recordings will be coded using Nvivo computer software (Mills, Bonner and Francis 2006). Data analysis will take a sequential-explanatory approach, combining both deductive and inductive methods to investigate whether the theory developed earlier in the project holds, but also being open to new data and emerging themes [31]. The concept of inductive thematic saturation [21] (Maykut and Morehouse 1994) will be applied and negative cases will be actively sought [44]. The consistency with which the coding is applied will be assessed on a fifth of the data [29]. Analytic meetings will be held with the research team to discuss validity. Data will be interpreted within the context of possible cause–effect pathways of the intervention.

### Criteria for progression to a future definitive randomised controlled trial of the intervention

Study processes are designed to be iterative, formative and adaptive [6]. However, there are certain criteria on which progression to a future, larger trial of intervention effectiveness is dependent. These are:
Recruitment
> 80% of general practices approached (i.e. 5/6)> 60% of GPs approached per practice (i.e. 2/3)> 50% of patients approached per practice (i.e. 20/30)Collection of outcomes
> 60% of patient-reported outcomes (questionnaire response rate)> 70% of patient questionnaire respondents providing written consent to case-note review> 70% of video recordings useable for observer ratings

Loss to follow up is expected to be minimal and is therefore not included as a ‘stopping criteria’.

The Chief Investigator, the Trial Steering Committee and the sponsor have the authority to stop or advise modifications to the feasibility trial.

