### Sampling

Six GP practices will be recruited from rural Devon and from each of the cities of Exeter and Plymouth, UK. A minimum practice size of 3000 patients will ensure sufficient numbers of eligible participants. (It is anticipated that there will be approximately 800 older patients with multimorbidity in an average 8000 patient practice [1]). Table 1 shows the participant inclusion and exclusion criteria. An average of three (total = 18 GPs), and at least 2, GPs per practice will be recruited. Patients aged 65 and above with known multimorbidity, defined as the presence of two or more long-term conditions (as specified in Table 1), will be approached.

**Table 1 Tab1:** Participant inclusion and exclusion criteria

Participant type	Inclusion criteria	Exclusion criteria
GPs	Only permanent GPs (partners and salaried) to avoid loss to follow-up.	Locum (sessional) GPs Trainee GPs (GPs will not be excluded based on less than full time working)
Patients	Patients aged 65 and above with known multimorbidity The condition should be one of^a^: angina or long-term heart problem; arthritis or long-term joint problem; asthma or long-term chest problem; blindness or severe visual impairment; cancer in the last five years; deafness or severe hearing impairment; diabetes; epilepsy; high blood pressure; kidney or liver disease; long-term back problem; long-term mental health problem; long-term neurological problem.	Temporary residents and vulnerable patients e.g. those recently bereaved, those with severe mental illness, severe cognitive impairment, end stage disease, communication difficulties e.g. physical impairment caused by a stroke as opposed to language barriers, a learning disability, or those unable to complete questionnaires or interviews for any other reason. (A minimum time for a condition to be ‘long-term’ will not be specified)

^a^This list was adapted from the English National General Practice Patient Survey [10]. Where dyads of conditions occur within the same organ system, e.g. anxiety and depression, these will only be counted once e.g. mental health problem

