### Analysis

#### Recruitment capability, consent and randomisation procedures, sample characteristics

The trial will determine whether it is possible to recruit appropriate study participants to test the intervention, or whether amendments are required ahead of a future trial. The flow of participants will be summarised in a Consort diagram. Numbers of eligible clusters, individual participants identified and randomised, recruitment rates and attrition will be recorded.

The search strategy used to identify potentially eligible patients will be tested on different practice databases with a view to finalising a generic, universal search algorithm. Anonymised data on ineligible patients will provide a profile of those frequently excluded. Consideration will be given to whether adaptations to the trial could be appropriate, to enable these patients to participate in a future study.

Any difficulties with meeting recruitment targets (6 practices; at least 2 GPs per practice; at least 5 patients per GP) will be documented. Field notes and correspondence with practices will enable the issues to be explored. Patients’ reasons for declining will be reviewed in light of recruitment procedures. For example, patients will use the pre-consultation questionnaire to indicate whether they received the information pack in the post. The extent to which over-recruitment is necessary will be reviewed, as will the importance of incentivising participants.

Randomisation procedures will be discussed at team meetings to inform amendments prior to a larger trial. For example, consideration will be given to randomising more practices to the intervention than to usual care, to gather more data regarding intervention implementation if required. Consideration will be given to initiating the study in each of the three sites sequentially (e.g. inner city, then urban, then rural) in order to increase trial management capacity. Consideration will be given to blinding the research team for data analysis in the future trial.

Rates of patient consent, to the use of questionnaire data, to video-recording ([12]; Asan and Montague 2014) and to case note review, will be evaluated. Numbers lost to follow-up will be reviewed; however, it is anticipated that this will be minimal. The study will determine whether there are differential drop-out or recruitment rates between intervention and control groups (indicative of selection bias).

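### The patient-recruitment progression criterion is set per practice with no rule for combining the six practices, so a go/no-go result at 60% recruitment depends mainly on an unstated choice

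*Protocol article*

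**What the plan says.** The protocol article's section on criteria for progression first calls the study processes iterative and adaptive. It then sets some criteria apart: "there are certain criteria on which progression to a future, larger trial of intervention effectiveness is dependent". The patient-recruitment criterion among them is "> 50% of patients approached per practice", glossed as 20/30. Nothing is said about combining the practices, whether as every practice, a set number of them, an average or a pooled total.

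The Sampling section states the recruitment aim on the total: "A total of 180 (minimum 120) potential patients will be identified across 6 practices, with the aim of recruiting at least half". The unit of 30 comes from the same section, which identifies "ten consecutive potential participants with pre-booked consultations with each of the three recruited GPs". The number of GPs can vary: "An average of three (total = 18 GPs), and at least 2, GPs per practice will be recruited". The analysis section on recruitment capability gives a further target of "at least 5 patients per GP".

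**The concern.** The aim concerns the whole sample, but the criterion meant to test it is written for one practice of about 30 patients. If each practice has to meet it, the decision becomes six small-sample tests that must all succeed. Chance and ordinary variation between practices can then defeat it although the study as a whole has recruited more than half. If the criterion is meant on average or on the total, that problem goes away, but the text does not say so.

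At stake is the go/no-go decision. A progression criterion is useful only if its result can be read off the data in one way. Here the same data could be called a pass or a fail according to a choice made after the counts are known. The threshold adds to this, because the percentage and the count printed beside it disagree.

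**Working it through.** **Inputs from the protocol.** Six practices; 10 patients for each of 3 GPs, so 30 per practice and 6 × 30 = 180 in total; threshold more than 50%, glossed as 20/30; aim at least half of 180, which is 90.

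**Assumptions (not in the protocol).** True recruitment rate *p* of 50% to 70%; practices independent of each other; intra-practice correlation of 0, 0.02 or 0.05.

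**1. The plan's own count.** The neighbouring glosses agree with their percentages: 5/6 = 83.3% exceeds 80%, and 2/3 = 66.7% exceeds 60%, and in each case the count is the smallest that does. For more than 50% of 30, the smallest count is 16 (53.3%). The stated 20/30 is 66.7%, so it is not reproduced. Reading the threshold as at least 50% would give 15, not 20.

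**2. Formulas.** Let *q* = P(X ≥ r), with X binomial (30, *p*).
- All six practices pass: *q*⁶.
- At least five of six pass: *q*⁶ + 6*q*⁵(1 − *q*).
- Pooled: P(Y ≥ 91), with Y binomial (180, *p*).
- With correlation ρ, X is beta-binomial with parameters *ps* and (1 − *p*)*s*, where *s* = (1 − ρ)/ρ.

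**3. More than 50% (r = 16), patients independent.**

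| True rate | One practice | All six | At least five of six | Pooled, ≥ 91/180 |
|---|---|---|---|---|
| 50% | 0.428 | 0.006 | 0.055 | 0.470 |
| 55% | 0.645 | 0.072 | 0.310 | 0.898 |
| 60% | 0.825 | 0.31 | 0.72 | 0.996 |
| 65% | 0.935 | 0.67 | 0.95 | > 0.99 |
| 70% | 0.983 | 0.90 | > 0.99 | > 0.99 |

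At 60%, for example, *q* = 0.8246, so *q*⁶ = 0.3145, and adding 6 × 0.8246⁵ × 0.1754 = 0.401 gives 0.716 for five of six.

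**4. Allowing for variation between practices (r = 16).**

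| True rate | All six, ρ = 0.02 | All six, ρ = 0.05 | Five of six, ρ = 0.05 | Pooled, ρ = 0.05 |
|---|---|---|---|---|
| 60% | 0.21 | 0.145 | 0.475 | 0.953 |
| 65% | 0.48 | 0.33 | 0.73 | 0.995 |
| 70% | 0.75 | 0.56 | 0.90 | > 0.99 |

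**5. Studies that recruit more than half overall but have a practice below threshold.** If all six reach 16, the total is at least 96, so passing in all six implies passing on the pool. At 60%, the chance that at least one practice falls short, given that the pooled criterion is met, is 1 − 0.3145/0.9959 = 0.68. With ρ = 0.05 it is 1 − 0.1447/0.9534 = 0.85.

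**6. The count as printed (r = 20), independent.** One practice passes with probability 0.29 at 60% and 0.73 at 70%. All six pass with probability 0.0006 and 0.15.

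**7. Check against the per-GP target.** Five patients for each of three GPs is 15/30, exactly 50%. A practice that just meets this target does not exceed 50%.

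**The case against.** A reader might infer that the protocol requires all six practices to pass, and so that the criterion usually fails at 60%. The document does not support that. The progression section states no such rule. The Sampling section uses *per practice* for an average of three GPs and spells out separately the floor that applies to every practice. The 30 is itself an average (10 patients times an average of 3 GPs), so the line could be the overall aim restated for a typical practice. On that reading it passes with probability 0.996 at 60%.

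This stands as an objection to the strong reading, but it does not settle the weaker one. The adjacent GP criterion, also per practice and glossed as 2/3, mirrors the floor of at least two GPs in each practice. Requiring it of each practice is therefore a fair reading too, and the text does not choose between them.

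The 60% rate is also an assumption. It is above the aim of at least half, but below the 66.7% implied by 20/30 and below the 180 patients that the Abstract says the study aims to recruit. At 65% or 70%, the all-six probability is 0.67 or 0.90, so the choice of reading matters less as recruitment improves.

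The recruitment analysis section says that difficulties in meeting targets will be documented and explored, which is close to a site review. That softens the point but does not remove it, because the progression section still makes progression dependent on the criterion.

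Finally, a per-cluster standard can be legitimate, and an article may leave operational detail to the full protocol. But the unit, percentage and count are all stated here. The percentage and count conflict, and the unit differs from that of the aim.

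**Conclusion.** The concern holds as a defect in how the criterion is specified. It does not show that the trial would fail its own rule. The criterion is written for a single practice, the aim for the total, and no rule links them. At an assumed true rate of 60% and independent patients, the pass probability for more than 50% runs from 0.31 (every practice) through 0.72 (five of six) to over 0.99 (pooled). At an assumed correlation of 0.05, the same readings give 0.145, 0.475 and 0.953. The gap narrows at higher rates. The mismatch between more than 50% and 20/30 is a separate plain error in the same line, and depends on no assumption. If 20/30 were required of every practice, the criterion would be practically out of reach at 60%. The pass probabilities rest on 30 approached in every practice, a common underlying rate, and the assumed rates and correlations.

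**What to change.** Restate the patient criterion as more than 50% of all patients approached across the recruited practices. Report each practice's rate and the range, and treat a practice below the threshold as a reason to review that site, not as failure of progression. In the same line, correct 20/30 or reconcile it with the percentage: at more than 50%, the count is 16 of 30 in one practice, or 91 of 180 overall. If the investigators do want a standard for each practice, they should say how many of the six must meet it.

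The cost is one line of wording. The downside is that a poorly recruiting practice can be offset by the others; the per-practice report would show this.
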